### Outcome measurement

Sleep quality will be measured by PSQI score [35]. PSQI contains seven domains with scores from 0 to 3, yielding a total score ranging from 0 to 21, where a higher score indicates poorer sleep quality. The reliability and validity of its Chinese version have been confirmed [36, 37]. PSQI will be assessed at baseline, immediately after treatment (i.e., 8 weeks from baseline) and at 4, 8 and 12 weeks after treatment.

#### Primary outcome measurement

The primary outcome will be the difference of the clinical response rates at 8 weeks from baseline between two groups. According to the academic literature review, response is defined as a reduction of PSQI global score ≥ 3 [38]. The clinical response rate will be the number of participants who achieve a reduction of PSQI global score exceeding 3 points divided by the total number of participants in each group and multiplied by 100%.

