**Methods/design:**

The proposed study is a multi-center, double-blind (participants and assessors), parallel-group RCT. A total of 112 participants with insomnia will be recruited from six hemodialysis centers in Guangzhou, China, and randomly allocated in a 1:1 ratio to receive auricular acupressure on either active points (AA group) or control points (points irrelevant to insomnia management, SAA group). The treatment will last for 8 weeks prior to a follow-up period of 12 weeks. Evaluation by blinded assessors at baseline, at 8 weeks (end of treatment) as well as at 4-week, 8-week and 12-week follow-ups (after intervention) will include Pittsburgh Sleep Quality Index (PSQI) scores and average weekly dose of hypnotics. The primary endpoint is clinical response rate (percentage of participants who reach a reduction of PSQI global score ≥ 3 in each group) at 8 weeks from baseline. Secondary endpoints include the changes in PSQI scores over time from baseline, as well as the changes in weekly dose of hypnotics.

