### Sample size estimation

In a pilot RCT conducted previously, the clinical response rates of AAT and sham AAT were 62.5% and 32.3%, respectively [22]. With these data, we used the following formula to calculate the estimated sample size [34].$$ \mathrm{N}\kern0.5em =\kern0.5em \frac{{\left({u}_{\alpha }+{u}_{\beta}\right)}^2\left(1+\raisebox{1ex}{$1$}\!\left/ \!\raisebox{-1ex}{$\mathrm{k}$}\right.\right)p\left(1-p\right)}{{\left({p}_e-{p}_c\right)}^2},\kern0.5em p\kern0.5em =\kern0.5em \frac{p_e+{kp}_c}{1+k} $$

In this formula, *k* (the ratio of allocation) = 1, *u*_a_ and *u*_*β*_ are 1.6449 and 1.2816, respectively, when 90% statistical power (*β* = 0.1) is required and a significance level of 5% (*α* = 0.05) is allowed. Here, *p*_e_ represents the incidence rate of the treatment group, while *p*_c_ represents that of the control group. Therefore, we will require at least 56 subjects in each group taking into account an allowed dropout rate of 15%. The results have been confirmed using PASS software 11.0 (NCSS, LLC, Kaysville, UT, USA) by tests for two independent proportions.

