For outcome measurement, PSQI is a well-validated, patient-reported questionnaire. But for now there is not a defined minimal clinically important difference (MICD) to reflect the changes in a clinical intervention that are meaningful for the patients. In some case, statistically significant difference has little clinical significance. Therefore, we adopted the response rate for the primary endpoint from a clinical trial published by [name], the author of the PSQI. He performed a comprehensive data review to set the criteria for response: participant with a change in PSQI of more than 3 points after treatment was defined as a response case [38]. In addition, the global PSQI score and scores of seven domains will be also analyzed as secondary outcomes in this trial.

The design of the trial minimizes the risk of bias by the following methods: (1) It is designed as a multi-center, double-blinded RCT. A central randomization method is applied to ensure completely random allocation and concealment. Both the patients and the assessors are blinded to the groups, (2) The sample size was estimated based on a previous pilot study [22], (3) The screening of participants is performed strictly to represent the population studied, (4) The manipulation of AAT is standardized and the practice of AAT is performed strictly under the guidance of authoritative clinical guidelines [40, 41]. A senior acupuncturist will be invited to train the research nurses from six sites and assess their competence, which will ensure the homogeneity of treatment and (5) The selected scale for outcome measurement is of good validity and reliability [42]. The investigators involved in the study will undergo a training course and have their role assigned clearly before the start of the trial.

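### The primary endpoint is given two incompatible cut-offs, a PSQI reduction of at least 3 and one of more than 3 points, and nothing says which one governs

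*Protocol article*

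**What the plan says.** The cut-off appears four times in the protocol article, twice each way.

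- Abstract, Methods/design: the primary endpoint is the "percentage of participants who reach a reduction of PSQI global score ≥ 3 in each group".
- Primary outcome measurement, definition sentence: "response is defined as a reduction of PSQI global score ≥ 3", citing reference 38.
- Primary outcome measurement, the very next sentence: the numerator of the rate is "the number of participants who achieve a reduction of PSQI global score exceeding 3 points".
- Discussion, on where the criterion came from, again citing reference 38: "participant with a change in PSQI of more than 3 points after treatment was defined as a response case".

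The primary comparison is "the difference of the clinical response rates at 8 weeks from baseline between two groups". Outcome measurement describes the scale: "PSQI contains seven domains with scores from 0 to 3, yielding a total score ranging from 0 to 21". Sample size estimation takes its two rates from the pilot, where "the clinical response rates of AAT and sham AAT were 62.5% and 32.3%, respectively". Neither that section nor the Background says which cut-off the pilot used.

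**The concern.** A total made of seven whole-point domain scores can change only by whole points. A reduction of more than 3 therefore means at least 4, and the two rules disagree on every participant whose reduction is exactly 3. One such participant is enough for the two rules to give different rates. Several are to be expected among 112, although that is not certain.

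This is the only primary endpoint, and the conflict sits in the paragraph that defines it. One sentence defines the responder and the next is the computation an analyst would program. If both stand until analysis, either could be presented afterwards as the pre-specified rule. A result close to the significance boundary could then depend on the choice.

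There is a second consequence. The 56 per group rests on the pilot rates. If those were counted under the rule that is not finally used, the sample size belongs to a slightly different endpoint from the one analysed.

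**Working it through.** **1. Reproduce the plan's figure.** Inputs from Sample size estimation: p_e = 0.625, p_c = 0.323, k = 1, and quantiles that "are 1.6449 and 1.2816, respectively, when 90% statistical power" is required; dropout 15%.

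p = (0.625 + 0.323)/2 = 0.474

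N = (1.6449 + 1.2816)² × 2 × 0.474 × 0.526 / 0.302² = 46.82, rounded up to 47 per group; 47/0.85 = 55.3, rounded up to 56.

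The stated 56 is reproduced. The cut-off does not appear in this formula; it enters only through the two rates.

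**2. What a change of rule does to the rates.** The documents give no distribution for PSQI change. Assumption: the change is normal and rounded to whole points, with the same SD in both groups, SD 2.5 to 4. At least 3 then corresponds to a latent reduction above 2.5, and at least 4 to one above 3.5. For each group the mean is set so that the pilot rate holds under one rule, and the rate is then read off under the other.

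Example, SD 3.5, pilot counted at ≥ 3: means of 3.62 and 0.89 give 62.5% and 32.3% above 2.5. Above 3.5 they give 51.3% and 22.8%.

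Pilot counted at ≥ 3, trial analysed at > 3:

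| SD | Active | Sham | Difference | Reclassified of 112 | Power, 47 per group, one-sided 5% |
|---|---|---|---|---|---|
| 2.5 | 46.8% | 19.5% | 27.2 | 16.0 | 88.8% |
| 3 | 49.4% | 21.4% | 28.0 | 13.4 | 89.4% |
| 3.5 | 51.3% | 22.8% | 28.5 | 11.6 | 89.8% |
| 4 | 52.7% | 23.9% | 28.8 | 10.2 | 90.1% |

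Pilot counted at > 3, trial analysed at ≥ 3:

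| SD | Active | Sham | Difference | Reclassified of 112 | Power, 47 per group, one-sided 5% |
|---|---|---|---|---|---|
| 2.5 | 76.4% | 47.6% | 28.7 | 16.4 | 90.0% |
| 3 | 74.3% | 45.0% | 29.3 | 13.7 | 90.5% |
| 3.5 | 72.7% | 43.1% | 29.6 | 11.8 | 90.7% |
| 4 | 71.5% | 41.7% | 29.8 | 10.3 | 90.9% |

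Differences are in percentage points, taken before rounding. Reclassified = 56 × (shift in active + shift in sham). For example, at SD 2.5 in the first table: 56 × (0.157 + 0.128) = 16.0.

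**3. Reference power.** With the pilot rates as they stand (difference 30.2 points), 47 per group and one-sided 5%, power is 91.2%. This uses pooled variance under the null and unpooled variance under the alternative, which is why it sits slightly above the plan's 90%. The cut-off therefore moves power by about 0 to 2 points in either direction of the mismatch.

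**4. Wider SD range.** Over SD 2 to 5, with the pilot at ≥ 3, the rates under > 3 run from 42.8% versus 16.9% to 54.7% versus 25.5%. The difference is 25.9 to 29.2 points and power 87.5% to 90.4%.

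**The case against.** The best defence is that the trial's conclusion hardly depends on the choice. The primary outcome is the between-group difference, which stays at 27 to 30 points under SD 2.5 to 4, and power stays near 90%. That stands. It limits the consequences but does not tell the analyst which participants to count.

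It could also be said that an analysis plan, not shown here, may settle the matter. But nothing has been left out: the article states the endpoint rule and states it both ways.

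Three stronger readings are tempting and not supported.

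- A reader might infer that at least 3 is the true rule and the other two statements are slips. The count is two against two. The rate sentence is the operative computation, and the Discussion is the only place that explains the origin of the criterion; it reports reference 38 as using more than 3. That reference is not at hand, so rewriting the Discussion to match the abstract could misreport it.
- A reader might blame the cut-off for a fall in power from 90% to the low 80s. Figures of that size come from a two-sided test: with the pilot rates unchanged and 47 per group, two-sided power is already 84.6%, and it becomes 81.2% to 83.1% under > 3 (SD 2.5 to 4, pilot at ≥ 3). The plan's quantile of 1.6449 is one-sided; that is a separate question.
- A reader might infer that the trial was sized for the wrong endpoint. The pilot's cut-off is unstated, so this is a query and not an established error.

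**Conclusion.** The point holds as an internal inconsistency in the definition of the single primary endpoint, and it must be fixed. The contradiction follows from the text alone; the size of its effect rests on the assumed rounded-normal change with a common SD. Under SD 2.5 to 4, each group's reported response rate moves by about 8 to 16 percentage points and about 10 to 16 of 112 participants change status, whichever rule the pilot used. The effect on the difference and on power is small. The severity comes from an endpoint that can be computed in two ways, each with textual support, and from materially different headline rates. It does not come from loss of power, and the documents give no ground for preferring one rule.

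**What to change.** 1. Check the cut-off actually used in reference 38 and the one used to count the pilot's 62.5% and 32.3%.
2. Choose one rule before any unblinded look, and state it identically in the abstract and in both sentences of Primary outcome measurement. The Discussion should report reference 38 as it reads and, if the trial's rule differs, say so.
3. State the pilot's cut-off in Sample size estimation. If it was the other rule, recount the pilot rates under the chosen one and restate the power for 56 per group.
4. Report the response rate under the other cut-off as a labelled sensitivity analysis.

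The cost is a short amendment, one look at the cited source and one recount of existing pilot data. Visits, assessments and recruitment are unaffected. The article gives the trial status as still recruiting, so the change can be made cleanly if the data remain blinded.

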#### Secondary outcome measurement

Secondary outcomes will be changes in PSQI scores (including global score and scores of each of the seven domains) at the end of treatment and at each follow-up visit compared with baseline.

As the trial will not exclude participants on hypnotics or plan a washout period due to ethics considerations, participants may maintain their dose of hypnotics or require hypnotic agents during the study. In this case, clinical physicians will prescribe estazolam (14 tablets each prescription, 1 mg each tablet) and instruct them to adjust the dose of hypnotics according to their sleep quality. The participants should return the unconsumed tablets at the end of the week or require another prescription as needed. The weekly dose of hypnotic agents will be reported and also serve as a secondary outcome.

#### Patient safety

All participants will undergo blood biochemical tests before randomization and at the end of follow-up. According to Blood Purification Standard Operating Procedure in China [39], maintenance hemodialysis (MHD) patients will undergo investigations including serum creatinine (SCr), blood urea nitrogen (BUN), total carbon dioxide (TCO_2_), potassium, calcium, phosphate, parathyroid hormone (PTH), albumin, hemoglobin and KT/V every 3 months. These parameters are all essential for monitoring the complications and adequacy of dialysis for MHD patients. We will utilize these data to assess their safety during the trial. Adverse events throughout the treatment and follow-up periods, regardless of relevance to the interventions, will be documented, reported to the Ethics Committee and dealt with using appropriate treatment.

### Withdrawal criteria

Participants will be withdrawn from the study in the following situations:When a participant asks to withdraw from the study, at any time, for any reasonWhen severe adverse events or reactions occur

The data of these participants will be collected and included in further analysis.

### Data collection and management

Data of demographic characteristics and baseline assessment will be collected by screeners when the patients are recruited. Clinical outcome measurement will be performed by assigned outcome assessors after the treatment is completed and during the follow-up period. Assessors of each center will undergo a training course to obtain the capability of using PSQI. Data regarding medicine prescription and any adverse events reported by patients will be collected by clinical physicians of the Hemodialysis Department.

A research coordinator of each center will conduct quality control of data collection and be responsible for data entry. The data manager will be responsible for initial data cleaning, identifying, coding and conversion into the proper format for data analysis. Data analysis will be performed by a biostatistician from the Evidence-based Medicine and Clinical Research Service Group.

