### Randomization and allocation concealment

Subjects will be randomly allocated into one of the two treatment arms in a 1:1 ratio: (1) treatment group (AA group) and (2) control group (SAA group). Central randomized allocation will be performed. Patients will be stratified based on six sites and randomly assigned to one of the two groups. The Chinese Clinical Trial Registry will generate the random number sequence using computer software, and will deposit the allocation sequence in ResMan^®^ Clinical Trial Management Public Platform, a web-based database. When a new participant is enrolled in the study, the research coordinator of each site will apply for the allocation information through this online system and assign participants to interventions accordingly. It is not possible to speculate on the allocation status of the participant before obtaining this information. The other personnel, including research nurses, assessors and clinical physicians, are not authorized to apply for random numbers. All processes will be recorded and saved appropriately.

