### Blinding

Both the participants and the assessors in this trial will be blinded to the allocation. AAT will be provided by trained nurses and manipulated by patients. The nurses and patients will be told that we are comparing two different treatment protocols (TPs), in which all auricular points involved are named as numbers with specific defined locations. We will have two nurses in each site assigned to perform the intervention. One will be responsible for providing TP A and the other for TP B. The assignment of nurses is done by drawing lots. The nurses will receive researcher training before the trial. They are required to perform auricular acupressure following the standard procedure, no matter what TP they are practicing. They are also required not to discuss the difference between the two TPs with patients. To avoid differences due to the Hawthorne and Rosenthal effect [26, 27], we will script the nurses to limit their interaction with the participants. Any additional questions will be directed to the research coordinator of each center. All results will be reported to another investigator responsible for assessing sleep quality in a clinical interview. The investigator will provide questionnaires to participants at the scheduled time for assessment. Clinical physicians of the Hemodialysis Department are allowed to prescribe estazolam (14 tablets each time) when patients require. At the end of the week, the patients should return the tablets left and obtain a new prescription if they need. All personnel will be properly assigned before the start of the trial.

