**Fig. 3 Fig3:**
[figure not shown]
A demonstration of interventions in the trial. **a** A map of auricular acupoints commonly used. **b** Ear-press seed (Wang Bu Liu Xing) applied in this trial. **c** Acupoints of both groups in the trial

In this trial, two research nurses for each center will be assigned to administer AAT to participants. They will gain approval from licensed acupuncturists through training and competence assessment before the start of the trial. They will provide AAT for patients during dialysis sessions for eight consecutive weeks. A standard procedure of AAT has been established as follows:Identify the ear points according to the TP directed by the research coordinator.Sterilize the involved area of the ear with 75% isopropyl alcoholAttach an adhesive plaster (size: 1.0 cm × 1.0 cm) with one bead (*Semen vaccariae*, globes approximately 2.0 mm in diameter; surface: smooth; colour: black; Taicheng Technology & Development Co., Ltd., Shanghai, China) embedded in each acupoint (Fig. 3b)Provide instructions to press the beads with appropriate strength (approximately 0.3–0.4 kg) and rate (one to two beats per second) for 1 min at each point [28]. This should be done three times during the day and once in the eveningThe plasters will be replaced with fresh ones every 2–3 days (usually on the dialysis day) depending on the dialysis schedule. If the plasters or beads become detached, participants should come to the hospital to receive fresh plasters. To improve their adherence to interventions, we plan to attach the auricular acupressure beads when the patients come for their scheduled dialysis and replace the beads every 2–3 days (on the dialysis day as well). Activities during each visit in the treatment period will be documented in the Case Report Form.

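### The site coordinator who holds each participant's allocation also checks and enters the outcome data, including the week-8 PSQI; separately, the article disagrees with itself on who takes baseline PSQI.

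*Protocol article*

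**What the plan says.** The article gives the research coordinator of each site four duties, in four places.

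- **Randomization and allocation concealment:** "the research coordinator of each site will apply for the allocation information through this online system and assign participants to interventions accordingly". The same section closes this route to everyone else: "The other personnel, including research nurses, assessors and clinical physicians, are not authorized to apply for random numbers".
- **Interventions, standard procedure (text after Fig. 3):** the nurse's first step is "Identify the ear points according to the TP directed by the research coordinator".
- **Blinding:** nurses work from a script, and beyond it "Any additional questions will be directed to the research coordinator of each center".
- **Data collection and management:** "A research coordinator of each center will conduct quality control of data collection and be responsible for data entry". No outcome is excepted.

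Blinding is claimed for participants and assessors only (Abstract and Blinding section).

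On baseline, the Abstract says "Evaluation by blinded assessors at baseline, at 8 weeks (end of treatment" and so on through follow-up. Data collection and management says "Data of demographic characteristics and baseline assessment will be collected by screeners when the patients are recruited", and reserves the outcome assessors for the period after treatment. PSQI training is described there for assessors.

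**The concern.** Withholding the allocation from nurses, assessors and physicians protects the outcome data only as far as the data stay with people who lack it. Here the data pass from the blinded assessor to the coordinator, who knows the arm. Quality control involves judgement: which forms to send back, which unclear answers to settle and how, which missing items to chase. If those judgements differ by arm, even without intent, the difference enters the dataset before the data manager sees it.

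The primary endpoint is sensitive to small changes because it dichotomises the PSQI change at a cut-off of about 3 points. A one-point change in a borderline score can turn a non-responder into a responder. The scale is also subjective, and the Discussion presents blinding as a main protection against bias.

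The baseline mismatch matters less. The endpoint is the change from baseline to week 8, so it should be clear who obtains the first value, and that person should be trained as the later assessors are.

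**Working it through.** The main point rests on comparing roles; the plan states no figure to reproduce.

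**1. Who knows the allocation, and who handles the week-8 PSQI**

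| Role | Access to allocation | Contact with week-8 PSQI |
|---|---|---|
| Participant | Declared blinded | Reports it (the Discussion calls the PSQI patient-reported) |
| Outcome assessor | Declared blinded; may not apply for random numbers | Collects it |
| Research nurse | May not apply; works with coded protocols | None stated |
| Research coordinator | Obtains it for each participant and directs the protocol | Quality control and data entry |
| Data manager | None stated | Initial cleaning and coding, after entry |

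Only the coordinator's row combines knowledge of the allocation with handling of the outcome. The data manager's cleaning does not undo this, because it starts from what has been entered.

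**2. Where in the data path the exposure lies**

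The order is: participant's report, assessor's collection, coordinator's check and entry, data manager's cleaning, biostatistician's analysis. The first two steps are blinded. The exposure begins at the third.

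**3. Scale**

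The document gives no error rate, query rate or distribution of PSQI change, so no bias can be computed. What follows from the stated sample size is the weight of one record: 1/56 = 0.0179, or 1.8 percentage points of an arm's response rate. The planned difference is 62.5 − 32.3 = 30.2 points.

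**4. Baseline: timing and effect**

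A global PSQI above 7 is an inclusion criterion, so baseline PSQI is known before enrolment. Allocation is requested only once a participant is enrolled and cannot be guessed before then. Whoever takes the baseline score cannot be influenced by the arm.

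Could a systematic baseline error still matter? Suppose every baseline score were one point too high. Assume that PSQI change is normal with the same SD in both arms, centred to reproduce the pilot response rates. The shifted rate is Φ(z + 1/SD), with z = Φ⁻¹(0.625) = 0.3186 and Φ⁻¹(0.323) = −0.4593. The exact cut-off drops out of this formula. The SD is an assumption, so a range is shown.

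| Assumed SD | Active arm | Sham arm | Difference (points) |
|---|---|---|---|
| No shift | 62.5% | 32.3% | 30.2 |
| 2.5 | 76.4% | 47.6% | 28.7 |
| 3.5 | 72.7% | 43.1% | 29.6 |
| 5 | 69.8% | 39.8% | 30.0 |

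Both response rates rise by about 7 to 15 points. The difference between arms, which is the primary outcome, changes by 0.2 to 1.5 points.

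**The case against.** **Nothing claimed is contradicted.** Blinding is asserted for participants and assessors, and both remain blinded. This stands. A reader might infer that blinded assessment does not cover the primary endpoint; the article does not support that, since the week-8 PSQI is reported and collected under blinding. The point is a conflict of duties after measurement.

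**The coordinator may see only the codes.** Treatments are called TP A and TP B with numbered points, and the article does not say whether coordinators know which is active. This stands in part. But the randomization section says the coordinator obtains the allocation information, the Discussion offers the coding as a means of blinding participants and practitioners, and no section counts the coordinator among the blinded. Even a coded label sorts participants by arm.

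**A condensed article leaves out safeguards.** Double entry, source verification and audit trails usually sit in a fuller document, and their absence here is no finding. That is right, and the point does not rest on it: the article positively gives both duties to one role.

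**Any figure for the bias is invented.** One could suppose that a quarter of borderline records are altered by one point, in opposite directions by arm. With an assumed SD of 3.5 that moves the difference by about 5 points. The arithmetic follows from its premises, but nothing in the document supports that rate or direction, so the figure is not relied on here.

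**Baseline by screeners breaks nothing.** Correct. A reader might infer a breach of blinding, or scores pushed up to meet the entry threshold. The first is excluded by timing. The second is speculation: the article says that screeners collect the data, not that they score the PSQI or raise it.

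**Conclusion.** The point holds as a stated conflict of duties. At each site the role that obtains and acts on the allocation also controls the quality of, and enters, the outcome data, including the week-8 PSQI. The exposure is confined to checking and entry. Its size cannot be derived from the document; the weight of a single record (1.8 points in an arm of 56) shows why the step deserves protection, not that bias will occur.

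This assumes the natural reading that the coordinator in the randomization section and the one in the data section are the same role at each site, and that data entry includes the PSQI, since no outcome is excepted.

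The disagreement between the Abstract and the data section on who takes baseline PSQI is real but secondary. It concerns consistency of administration, and under the assumptions shown it leaves the difference between arms nearly unchanged.

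**What to change.** Amend Data collection and management so that PSQI and other outcome data are entered and checked by existing staff without allocation access. For example, the blinded assessor enters the questionnaire and the data manager handles queries. Limit the coordinator to allocation, scheduling and non-outcome data.

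Set database permissions so that whoever enters or checks outcomes cannot see the allocation. This needs explicit attention if outcomes go into the web platform that holds the allocation sequence; the article does not say whether they do.

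Reconcile the Abstract with the data section on baseline. Preferably the trained assessor gives the PSQI at baseline, before randomization, as at the four later time points. If screeners keep the task, the Abstract should say so and the PSQI training should include them.

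The cost is a few minutes of entry per visit for the assessor, one more questionnaire per participant if baseline moves to the assessor, and a change of permissions. Recruitment is described as ongoing, so the change would protect only data still to be entered; the report should state when it took effect.
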